#### Criteria for discontinuing or modifying allocated interventions {11b}

Criteria for discontinuing study protocol are as follows:
Unexpected conversion of MITS to open thoracotomyUnexpected regional anaesthesia complicationSuspected or confirm diagnosis of local anaesthesia toxicityUnexpected postoperative admission to the intensive care unitInability to place ESP or PVB catheterPatient request to be withdrawn from the studyClinical concern of patient’s care from surgical, anaesthesia or research team

#### Strategies to improve adherence to interventions {11c}

A study flow chart (Fig. 1) and analgesia and anti-emetic protocol (Fig. 2) will be made available in the operating theatre, surgeons and anaesthesiologist performing the intervention, postanaesthesia care unit (PACU) department and data collectors for the purpose of protocol adherence.

**Fig. 2 Fig2:**
[figure not shown]
Analgesia and anti-emetic protocol

### Relevant concomitant care permitted or prohibited during the trial {11d}

All patients will undergo general anaesthesia (GA) as part of the standard of care for their video-assisted thoracic surgery. Intravenous induction of GA will be conducted or supervised by a consultant anaesthesiologist. Induction of GA will be achieved by administrating intravenous fentanyl, oropofol and a neuromuscular blockade agent at the discretion of the anaesthesiologist. An analgesia and anti-emetic concomitant care plan will be standardised for the pre-surgical, intraoperative, PACU and postoperative periods. This is outlined in Fig. 2.

### Provisions for post-trial care {30}

Patients that are enrolled into the study are covered by indemnity for negligent harm, through the standard Health Service Executive (HSE) indemnity arrangements. If any participant suffers from any complications arising directly from either intervention, he/she will receive standard postoperative management which may include from the surgical team, pain medicine department and allied health care professions. In addition, all investigators in all potential clinical sites will be respective employees of the hospital and covered by the clinical indemnity scheme.

### Outcomes {12}

#### Primary outcome

The primary outcome in this study is the Quality of Recovery (QoR-15) score between anaesthesiologist-administered ultrasound-guided erector spinae block and surgeon-administered video-assisted paravertebral block at 24 h postoperative. This score is a measure of overall postoperative recovery across five dimensions of health: patient support, comfort, emotions, physical independence and pain [17].

#### Secondary outcome measures

The following secondary outcomes will be measured:
Chronic persistent surgical pain (CPSP) after minimally invasive thoracic surgery (MITS) at postoperative day 90 (this will be achieved by assessing the patient for chronic pain by using the Brief Pain Inventory (BPI) Short Form and Short Form McGill (SF-15) questionnaires)Pulmonary function assessment ( this will be evaluated preoperatively and at postoperative days 1 and 2 using a bedside incentive spirometry)Area under the curve (AUC) of Verbal Rating Score (VRS) for pain at rest and on deep inspiration versus time over 48 hTime taken to site ESP and PVB catheterTime of administration of first intravenous opioidTotal 24- and 48-h morphine-equivalent consumptionNausea, vomiting and pruritisRegional anaesthesia block-related complications (e.g. block failure and catheter dislodgement)Duration of postanaesthesia care unit (PACU) stayLength of hospital stay and QoR-15 at 48 hSummary of postoperative complications (this will be measured by calculating the Comprehensive Complication Index (CCI) at postoperative day 30)

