### Objectives {7}

Our main aim and corresponding hypotheses are outlined below.

We will conduct a randomised controlled clinical trial comparing the efficacy of anaesthesiologist-administered, ultrasound-guided ESP catheter analgesia to surgeon-administered, video-assisted PVB catheter analgesia. We will test the hypothesis that anaesthesiologist-administered ultrasound-guided ESP catheter analgesia is equivalent to surgeon-administered, video-assisted PVB catheter analgesia, in terms of early Quality of Recovery (QoR-15) and postoperative respiratory spirometric function at 24–48 h and CPSP at 3 months after MITS surgery.

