### Sample size {14}

The established minimum clinically important difference (MCID) in QoR-15 score after surgery is 8.0 [18], and the *SD* of QoR-15 scores is typically between 10 and 16 [range of QoR score is 1–150]. Therefore, we considered a reduction in mean QoR-15 scores by 8 to be clinically meaningful and used this value as our delta (Δ) limit. In addition, we have chosen a standard deviation (*SD*) of 12 to reflect our study population. Based on these assumptions, we considered the following for our sample size analysis. For a two-sided test, assuming a type I error (*α*) = 0.05 and type II error (*β*) = 0.2, a sample size of *n* = 36 per group will have 80% power to detect a statistically significant difference in mean QoR-15 scores.

We aim to enrol *n* = 40 each group to allow for loss to follow-up, missing data or withdrawal of consent. The sample size was estimated using the following formula [19]: *n* = 2*σ*^2^ (*z*1 − *α*/2 + *z*1 − *β*)^2^/Δ^2^, where *α* and *β* are the probabilities of type I and II errors, *σ* is the *SD* and Δ is the delta limit. This calculation was subsequently verified by an online calculator (Georgiev G.Z., “*Sample Size Calculator*”, Available at: https://www.gigacalculator.com/calculators/power-sample-size-calculator.php).

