The key secondary outcomes that will be measured in this trial include the following: chronic persistent surgical pain (CPSP), postoperative respiratory function, Verbal Rating Score (VRS) and measure of postoperative complications. CPSP will be assessed at postoperative day 90 by using the Brief Pain Inventory (BPI) form and Short McGill form (SF-15) questionnaires. The designated data collector will complete these questionnaires by telephone follow-up with the study participant. BPI assesses the pain intensity (scale 0–10) and interference of pain (scale 0–10) on quality of life. It was originally developed to assess cancer pain. However, it has been validated for its use in the assessment of chronic pain in the non-malignant pain population [22, 23]. The SF-15 questionnaire is a shorter version of the original McGill Pain Questionnaire. It consists of a pain rating index which has two subscales: sensory subscale with 11 words and affective subscale with 4 words. The SF-15 is a highly valid tool to evaluate pain in patients with and without neuropathic aetiology [24, 25]. Postoperative respiratory function will be assessed by measuring the patient’s average maximum inspiratory effort, by using a bedside incentive spirometer. This parameter will be gauged by the designated data collector at three time points. These time points include the preoperative period (prior to induction of general anaesthesia) and at postoperative days 1 and 2. Area under the curve (AUC) of Verbal Rating Score (VRS) for pain at rest and on deep inspiration versus time over 48 h postoperative will be measured. This method is an accepted approach for enhanced interpretation of pain outcomes for patient care [26]. Finally, the Comprehensive Complication Index (CCI) will be used to summarise the frequency and severity of all postoperative complications. This method of measuring surgical morbidity is more sensitive than existing morbidity endpoints and it is accepted as an applicable primary endpoint in surgical trials [27]. The data collectors for this trial will retrospectively review paper and electronic medical records up to postoperative day 30 and subsequently compute the CCI score according to the established Clavien-Dindo classification (available at www.assessurgery.com). The CCI score ranges between 0 (no complication) and 100 (death).

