### Statistical methods

#### Statistical methods for primary and secondary outcomes {20a}

The collected raw data will be initially inspected for any errors; this includes but is not limited to double entry errors, missing data and data that was incorrectly entered. Data will be analysed by GraphPad Prism version 8 (GraphPad, Salt Lake City, UT, USA). The data will be tested for normal distribution according to the Shapiro-Wilk test. Primary and secondary outcomes will be analysed as follows: normally distributed data will be compared between the two groups using the unpaired Student *t* test and non-normal distributed data will be compared by using the Mann-Whitney *U* test. All data will be summarised as mean ± *SD* or median (25–75% range) as appropriate, and *p* value < 0.05 will be considered statistically significant.

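### Spirometry is measured before surgery, but the tests named for it take no baseline covariate; adjusting for the preoperative value would sharpen a key secondary comparison without new data

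*Protocol article*

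**What the plan says.** The Objectives section {7} puts spirometry in the trial hypothesis. Equivalence is to be tested for QoR-15 and for "postoperative respiratory spirometric function at 24–48 h and CPSP at 3 months after MITS surgery". The section on assessment and collection of outcomes {18a} counts respiratory function among the key secondary outcomes and defines the measurement: "Postoperative respiratory function will be assessed by measuring the patient’s average maximum inspiratory effort, by using a bedside incentive spirometer".

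A baseline is scheduled in two places. The list of secondary outcome measures says that "this will be evaluated preoperatively and at postoperative days 1 and 2 using a bedside incentive spirometry". Section {18a} repeats it: "These time points include the preoperative period (prior to induction of general anaesthesia) and at postoperative days 1 and 2".

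The statistical methods section {20a} has one rule for all primary and secondary outcomes, applied after a Shapiro-Wilk test: "normally distributed data will be compared between the two groups using the unpaired Student" t test, while "non-normal distributed data will be compared by using the Mann-Whitney" U test. The article mentions no ANCOVA, mixed model, change from baseline or percentage of baseline. Its Discussion explains why QoR-15 has no preoperative value, but that explanation does not concern spirometry.

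**The concern.** Inspiratory effort differs widely between people for reasons unrelated to the block. The trial admits both sexes, ages 18 to 85 and ASA grades 1 to 4, and the outcome is not described as a percentage of a predicted value. Much of the spread in the day 1 and day 2 readings may therefore be spread that was already present before surgery. A two-sample test on the postoperative readings leaves that spread in the standard error, although the trial has recorded the number that would remove part of it.

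This outcome carries an equivalence hypothesis, and there the width of the confidence interval decides what can be concluded. Precision given up here bears directly on that question.

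**Working it through.** **The plan's own figure.** The only sample size in the article is for QoR-15. It takes a two-sided α of 0.05, β of 0.2, SD 12 and Δ = 8 ("we considered a reduction in mean QoR-15 scores by 8 to be clinically meaningful and used this value as our delta"). The stated formula gives

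n = 2 × 12² × (1.960 + 0.842)² / 8² = 35.3, rounded up to 36 per group.

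This agrees with the article, and 36 / 0.90 = 40 agrees with the enrolment target. No power figure is stated for spirometry, and nothing below alters the 36 or the 40.

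**Inputs for spirometry.** From the documents: 40 per group, 1:1 allocation, one preoperative reading, and readings on days 1 and 2. Not in the documents: the correlation r between the preoperative and a postoperative reading. I assume a range of 0.3 to 0.8.

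**Formulas.** These are large-sample variances of the treatment difference, relative to a comparison of raw postoperative values, with equal SD before and after surgery assumed for the change score:

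- raw postoperative value: 1
- change from the preoperative value: 2(1 − r)
- ANCOVA on the preoperative value: 1 − r²
- ANCOVA relative to the change score: (1 − r²) / [2(1 − r)] = (1 + r)/2

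The CI narrows by 1 minus the square root of the relevant ratio. The equivalent number per arm, against raw values, is 40 / (1 − r²).

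| Assumed r | ANCOVA ÷ raw variance | CI narrower than raw | 40 per arm worth | Change ÷ raw variance | ANCOVA ÷ change variance | CI narrower than change |
|---|---|---|---|---|---|---|
| 0.3 | 0.91 | 5% | 44 | 1.4 | 0.65 | 19% |
| 0.5 | 0.75 | 13% | 53 | 1.0 | 0.75 | 13% |
| 0.7 | 0.51 | 29% | 78 | 0.6 | 0.85 | 8% |
| 0.8 | 0.36 | 40% | 111 | 0.4 | 0.90 | 5% |

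Example at r = 0.7: 1 − 0.49 = 0.51; √0.51 = 0.714, so 29% narrower; 40 / 0.51 = 78. Against change: (1 + 0.7)/2 = 0.85; √0.85 = 0.922, so 8% narrower.

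**In terms of power.** Take a spirometry difference that the unadjusted comparison would detect with 80% power at 36 per group. With ANCOVA the power becomes about 84%, 90%, 97.5% and 99.7% at r = 0.3, 0.5, 0.7 and 0.8.

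The change-score column also shows that subtracting the baseline is not a safe substitute: below r = 0.5 it is less precise than using the raw value. ANCOVA is at least as precise as either at every r in the range.

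**The case against.** The strongest reply is that {20a} does not say which spirometry variable is tested. *Unpaired* describes a comparison of two groups; an unpaired t test on the change, or on the percentage of the preoperative value, would fit the wording. A reader might infer that the plan ignores the baseline, but the article does not state that. It shows only that no role is given to the baseline and that the named tests have no covariate. This part of the objection stands, and so the table carries both readings. It does not remove the point, because ANCOVA is the more precise choice under either.

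A second reply is that {20a} is a generic sentence in a condensed article, and that details for one secondary outcome belong in an analysis plan that is not shown. That would hold if the article were silent. It is not: it names the tests for all secondary outcomes, and an analysis plan that followed it would have no baseline term.

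A reader might also infer that chance baseline imbalance biases the result. It does not. Allocation is randomised, so the unadjusted estimate is unbiased, and the usual standard error already allows for such imbalance.

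Finally, the size of the gain rests on an assumed correlation. At r = 0.3 the gain against raw values is only 5%, and the 40% figure needs both r = 0.8 and a raw-value comparison. This too stands. So does the remark that the article states no equivalence margin for spirometry; that is a separate matter, which baseline adjustment does not settle.

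**Conclusion.** The point holds as one of efficiency. For a key secondary outcome named in the hypothesis, the article fixes tests without a covariate although a preoperative value is scheduled for each patient. The analysis is valid but less precise than it could be.

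Over r = 0.3 to 0.8, the avoidable width of the confidence interval is about 5% to 40% if raw postoperative values are compared, and about 19% down to 5% if change scores are. These figures rest on the assumed r, on large-sample formulas and, for change scores, on equal SDs before and after surgery. That the method is sound in principle and its improvement certain in direction does not depend on them.

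The documents do not support a claim of bias, a single headline gain, or any consequence for the primary outcome or the sample size.

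**What to change.** Add one sentence to the statistical methods section {20a}, for example: *Spirometry on postoperative days 1 and 2 will be compared between groups by ANCOVA, or by a mixed model over both days, with the preoperative value as covariate; the adjusted mean difference and its 95% CI will be reported.* Choose one of the two models before the data are unblinded.

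State that for this outcome the sentence replaces the choice between t test and Mann-Whitney U test by a normality test. This also settles which quantity is analysed.

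The cost is the wording, plus a check that the chosen software can fit the model. It needs no additional patients, visits or measurements.

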#### Other study parameters

The following data will also be collected: patient gender, age, height, weight, American Society of Anaesthesiologist (ASA) grade and type of surgery.

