### Trial design {8}

This manuscript outlines a research protocol for a double-blind, randomised controlled, equivalence trial. This study is designed as equivalence, as the analgesic effectiveness of a successful paravertebral block is not questioned. Patients that volunteer to participate in this clinical trial will be equally (1:1) and randomly allocated into one of two intervention groups: anaesthesiologist-administered ultrasound-guided erector spinae catheter group (ESP catheter group) or surgeon-administered, video-assisted paravertebral block catheter group (PVB group). Figure 1 illustrates the study flow chart. Recruitment commenced on 12 May 2021, and it is expected to take between 9 and 12 months for completion.

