#### Methods in analysis to handle protocol non-adherence and any statistical methods to handle missing data {20c}

The primary outcome will be assessed using an unpaired Student *t* test analysis or Mann-Whitney *U* test, depending on data distribution. Given our expectation that very few patients will be lost to follow-up during their inpatient stay and protocol adherence strategies as mentioned above, we expect missing data will be reduced to a minimum when analysing the primary outcome. If a statistical method is needed to account for missing data in the secondary outcomes (e.g. CPSP survey at 3-month follow-up), multiple imputation will be used.

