This protocol will result in the anaesthesiologist and surgeon not being blinded to the group allocation as they will be required to perform the block. However, the primary outcome is the QoR-15 score at 24 h postoperatively which will be measured by researchers blinded to the group allocation. We have chosen to exclude patients with existing chronic pain conditions or with a history of opioid abuse. The justification for this decision comes from the fact that these patients are more likely to develop postoperative chronic pain and so the results of our 3-month chronic pain scores may be affected by the inclusion of these patients. Pain scores and quality of recovery will be recorded up to 48 h postoperatively. We acknowledge that for some patients having MITS their recovery will continue beyond 48 h; however, the acute postoperative pain following MITS is reduced by day 3 and many of our patients are discharged home at this stage. Length of stay and postoperative complications will continue to be observed after this timeframe and patients will be followed up until 3 months postoperatively. Paravertebral and ESP catheters will be placed under general anaesthesia; therefore, formal dermatomal assessment of block function will not be undertaken. Therefore, we will not be formally testing block effectiveness. However, the practice of placing these catheters under ultrasound guidance or thorascopic vision after induction of general anaesthesia is in line with common clinical practice, and therefore, our findings should still be applicable to widespread clinical practice. Patients’ preoperative QoR-15 will not be assessed in this study. Therefore, we will not have a baseline from which to compare postoperative QoR-15 scores. However, QoR-15 was designed specifically for postoperative use, and we will apply this scoring tool to both randomised cohorts equally. Moreover, the ability of QoR-15 in the immediate preoperative period to give an accurate baseline has been questioned [37]. By focusing on patient-centred outcomes in our trial design, we hope to elucidate whether these relatively straightforward fascial plane blocks can enhance recovery and improve safety for patients by reducing postoperative morbidity and complications.

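### Spirometry has a preoperative value that the stated tests do not use; ANCOVA on it, and optionally covariate adjustment of QoR-15, would add precision at little cost

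*Protocol article*

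**What the plan says.** Statistical methods {20a} applies one rule to primary and secondary outcomes alike: an unpaired t test if the data look normal, otherwise a Mann-Whitney U test, with significance at p below 0.05. Section {20c} repeats it for the primary outcome: "The primary outcome will be assessed using an unpaired Student *t* test analysis or Mann-Whitney *U* test, depending on data distribution". Neither section mentions a covariate or a baseline value.

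The baseline data are as follows.

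- Spirometry, under Secondary outcome measures: "this will be evaluated preoperatively and at postoperative days 1 and 2 using a bedside incentive spirometry". Section {18a} confirms the three time points, and Objectives {7} names spirometric function at 24–48 h in the equivalence hypothesis.
- Other study parameters: "patient gender, age, height, weight, American Society of Anaesthesiologist (ASA) grade and type of surgery". No analysis role is given.
- QoR-15 has no baseline. The Discussion says: "Patients’ preoperative QoR-15 will not be assessed in this study".

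Trial design {8} describes a "double-blind, randomised controlled, equivalence trial". Sample size {14} sets the limit: "we considered a reduction in mean QoR-15 scores by 8 to be clinically meaningful and used this value as our delta (Δ) limit". Sequence generation {16a} uses blocks of 10 and names no stratification factor.

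**The concern.** In an equivalence trial the conclusion depends on how narrow the interval for the difference is. Two sources of precision are already being collected and have no stated use.

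The stronger one is preoperative spirometry. Inspiratory capacity before surgery differs widely between patients for reasons unrelated to the block, and a comparison of postoperative values alone carries all of that variation as noise.

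The weaker one is the set of patient characteristics that might predict 24 h QoR-15. The eligible population is broad (age 18–85, ASA 1–4, VATS and RATS), and neither the randomisation nor the analysis accounts for these factors. At stake is precision only. The comparison is not biased.

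**Working it through.** **The plan's own figure.** Section {14} gives n = 2σ²(z₁₋α/₂ + z₁₋β)²/Δ². With σ = 12, Δ = 8, two-sided α = 0.05 and β = 0.2, n = 2 × 144 × (1.960 + 0.842)²/64 = 35.3, so 36 per group as stated. The formula is for detecting a difference and has no covariate term.

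**Spirometry.** Let σ² be the variance of the postoperative value and ρ its correlation with the preoperative value. The article gives no ρ, so 0.5–0.7 is assumed. The change-score row also assumes equal variance before and after surgery.

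| Comparison | Variance | ρ = 0.5 | ρ = 0.7 |
|---|---|---|---|
| Raw postoperative value | σ² | 1.00σ² | 1.00σ² |
| Change from preoperative | 2σ²(1 − ρ) | 1.00σ² | 0.60σ² |
| ANCOVA | σ²(1 − ρ²) | 0.75σ² | 0.51σ² |

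ANCOVA therefore cuts variance by 25–49% against raw values. Against change scores the ratio is (1 + ρ)/2, a cut of 25% at ρ = 0.5 and 15% at ρ = 0.7. With 72 patients, the expected cost of estimating one slope is a factor (N − 3)/(N − 4) = 69/68, about 1.5% of variance.

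**QoR-15.** Inputs from {14}: SD 12, limit 8, 36 per group (N = 72). Assumed: true difference 0, two one-sided 5% tests, and R² for the covariates, for which the documents give no figure. With k covariate degrees of freedom:

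- residual SD = 12 × √(1 − R²)
- expected inflation of variance from chance imbalance = (N − 3)/(N − 3 − k); for k = 3 this is 69/66 = 1.045
- 90% half-width = t₀.₉₅ on (70 − k) df × residual SD × √inflation × √(2/36)

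Unadjusted: 1.667 × 12 × 0.2357 = 4.71. At k = 3 and R² = 0.10: 1.668 × 12 × √(0.90 × 1.045) × 0.2357 = 4.58. Power is t-based and allows for estimation of the SD.

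| Analysis | Assumed R² | 90% half-width | Power |
|---|---|---|---|
| Unadjusted | – | 4.71 | 75% |
| k = 3 | 0 | 4.82 | 73% |
| k = 3 | 0.05 | 4.70 | 76% |
| k = 3 | 0.10 | 4.58 | 79% |
| k = 3 | 0.20 | 4.31 | 84–85% |
| k = 3 | 0.30 | 4.04 | 90% |

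Break-even is at R² of about 0.04–0.05. Three degrees of freedom means age, ASA grade as a linear score and a two-level type of surgery. With ASA 1–4 as categories, k = 5, the inflation is 69/64 = 1.078 and break-even rises to about 0.07.

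**The case against.** The other side has a good case on QoR-15. An unadjusted comparison is valid in a 1:1 randomised trial, no stratification factor is named that the model would have to carry, and the sample size was set for an unadjusted test. Chance imbalance is already allowed for in that test's error rates. A covariate model may also stand in an analysis plan that is not shown. All of this stands, and it makes the QoR-15 part an option.

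Three stronger readings might be inferred, and the documents support none of them.

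- *The planned equivalence interval is likely wider than it need be.* The article states no interval, no two one-sided tests and no comparison with ±8. Its criterion is a difference test at p below 0.05, which cannot establish equivalence and is a separate, more serious matter. The word likely would also need an R² that the documents do not give.
- *Age, ASA grade and type of surgery are the only usable baseline variables.* Gender, height, weight and preoperative spirometry are collected too. Type of surgery is not defined under Other study parameters. It may mean VATS or RATS, or the kind of resection with more levels.
- *Spirometry is analysed ignoring the preoperative value.* Section {20a} names the test but not whether it is applied to raw values or to change. A t test on change would use the baseline. Even so, ANCOVA is at least as precise as either, apart from the small cost of one degree of freedom.

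At the enrolment target of 40 per group with no losses, unadjusted power is already about 81%, which further limits the need for adjustment.

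**Conclusion.** The point holds as a matter of efficiency; the plan contains no error or contradiction here. The spirometry part is firm: the outcome's own baseline is measured, the outcome is in the equivalence hypothesis, and ANCOVA would cut variance by 25–49% against raw values if ρ is 0.5–0.7. The article gives no limit for spirometry, so this cannot be turned into power.

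The QoR-15 part is modest. The half-width is about 3% narrower at R² of 0.10 (4.58/4.71) and about 8% at 0.20 (4.31/4.71). There is no material gain at about 0.05, and a loss of 2–3 points of power if the covariates explain nothing. It matters only once the difference test has been replaced by an interval-based equivalence analysis.

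**What to change.** 1. Spirometry: analyse day 1 and day 2 values by ANCOVA with arm and the preoperative value, and report the adjusted difference with its confidence interval. Cost: one degree of freedom and a change of wording.
2. QoR-15, optional: before unblinding, prespecify a linear model for the 24 h score on arm plus a few collected covariates, for example age, ASA grade and type of surgery. State how ASA grade is coded and what type of surgery means. Report the adjusted difference and interval against ±8, and keep the unadjusted comparison as a sensitivity analysis. Cost: three degrees of freedom, or about five with ASA grade as categories.
3. Make item 2 part of replacing the p < 0.05 difference test with an interval-based equivalence analysis, since it has little purpose without that.

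No new data are needed.
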